For many women with severe/morbid obesity, bariatric surgery^[26,27]^ is the first step towards a change in their lifestyle and quality of life, as it significantly reduces excess weight^[28]^ and promotes the remission of metabolic syndrome, hypertension or type 2 diabetes,^[29]^ which in turn significantly decreases the incidence of morbidity–mortality.^[30,31]^ Bariatric surgery seems to improve a woman's ovarian function by reducing the free androgen index, partially improving the luteal function,^[32]^ regulating the menstrual cycle (by increasing follicle-stimulating hormone [FSH] and LH, and decreasing testosterone and Dehydroepiandrosterone sulfate [DHEA-S]), improving conception rates and reducing the incidence of early abortions.^[33]^ However, other authors indicate that by increasing the rate of maternal malabsorption (depending on the surgical technique) and decreasing the ovarian reserve by decreasing levels of Anti-Müllerian hormone,^[34,35]^ fertility could continue to be compromised following bariatric surgery. Moreover, the success of bariatric surgery and the evolution of the patient in the short, (and above all) medium and long term is strongly determined by their post-operative lifestyle.^[36]^ About 50% of patients regain weight in the 24 months after surgery^[37]^ and may again have complications associated with severe/morbid obesity.^[38,39]^ It is therefore of great clinical and public health importance to study the effectiveness of complementary interventions aimed at improving the lifestyle of the obese patient from the first year of bariatric surgery in order to understand the effects of these changes in ovarian function and reproductive capacity, compared to the usual post-operative treatment.

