Other proposed mechanisms implicated in the relationship between obesity and reproductive problems, such as chronic inflammation^[53]^ or arterial stiffness,^[54]^ could also be significantly improved through exercise in this population. Recently, Stolberg et al^[55]^ found no improvement in inflammation following a training program initiated 6 months after bariatric surgery (70% women), although program adherence was clearly insufficient (i.e., only 59.4% of the participants attended 50% or more sessions) and the insufficient details about the intervention compromises replicability and the quality of the study.^[56]^ Therefore, the extent to which exercise, started immediately after surgery, can improve inflammation and arterial distensibility, and whether changes in these parameters can mediate possible improvements in women's ovarian function remain to be investigated.

For all of the above, studying the effectiveness of a supervised concurrent (strength and aerobic) exercise programme on the ovarian function of women undergoing bariatric surgery, both in the short (16 weeks) and medium (12 months) term, is of great clinical and social interest, especially considering the significant ovulatory problems that obesity confers. We postulate that a supervised evidence-based exercise program following the *Consensus on Exercise Reporting Template* (CERT),^[57,58]^ significantly improves ovarian function following bariatric surgery.

Thus, the main aim of the EMOVAR clinical trial is to examine, over the short (16 weeks) and medium (12 months) term, the effects of a supervised physical exercise program (focused primarily on aerobic and resistance training) on ovarian function in women with severe/morbid obesity who have undergone bariatric surgery, in comparison with usual care following bariatric surgery. Secondary aims are to examine the effects of the intervention on chronic inflammation and insulin resistance, arterial stiffness, physical fitness and health-related quality of life. We will also assess whether changes in inflammatory parameters, insulin resistance or arterial stiffness, induced by exercise, are associated with changes in ovarian function. Finally, the extent to which changes in body weight and composition, or changes in physical fitness (i.e., aerobic capacity and muscular strength), induced by the training program, are associated with changes in ovarian function will also be investigated.

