### Randomization

2.4

The patients will be randomly assigned either to supervised physical exercise (exercise group; EG) or to a usual care control group (CG). A simple computer-generated randomization sequence^[60]^ will be obtained, representing the allocation of each participant. Individual allocations will be held into a sealed, opaque envelope and numbered in sequential order corresponding to the order in which the participants will be randomized. Each participant will be randomized (the corresponding envelope will be opened in front of the patient) at medical discharge following bariatric surgery, provided the participant has previously met the inclusion criteria, signed the informed consent, and performed baseline assessments (pre-test; Fig. 2). All study-related information will be stored securely at the study site. All laboratory specimens, reports, data collection, process, and administrative forms will be identified by a coded ID (identification) number to maintain participants’ confidentiality. All records that contain names or other personal identifiers, such as locator forms and informed consent forms, will be stored separately from study records identified by code number and only accessible by the principal investigators.

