#### Assessment calendar

2.6.1

Figure 2 graphically represents the data-collection planning that each enrolled participant will complete throughout the study. All participants will complete the whole battery of assessments at three time points (i.e., at baseline or pre-test [T1], within ∼12 days before the surgery; week 16 or post-test [T2], within a margin of 3 to 12 days following the intervention completion; and 12 months or follow-up [T3], within a 15 day margin).

Each of the 3 full clinical assessments (pre-test, post-test, and 12-month follow-up) consists of 4 visits (Table 2). In addition, participants in both groups will continue their protocol of regular visits to the surgical and nutrition clinics during the study (months 1, 3, 6, and 12 after surgery), in which participants from both groups (EG and CG) will receive lifestyle recommendations including internationally accepted physical activity and nutrition recommendations.^[27]^

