### Statistical analysis

2.11

Despite randomization, the between-group baseline comparability will be checked. Normal distribution of continuous quantitative variables will be graphically inspected using histograms, and—when needed—normality tests will also be used. The between-group differences in the change (post–pre) in the primary and secondary effects (the main and secondary objectives 1, 2, and 3) will be analysed using a general linear model (in the case of significant deviation from normality, we will proceed with non-parametric techniques, such as quantile regression). The effect size (95% confidence interval) and the level of statistical significance will be displayed. In order to demonstrate the clinical efficacy of the supervised exercise program on ovarian function after bariatric surgery, the main analysis will be a per-protocol analysis (i.e., it will only include participants who attend at least 80% of the exercise sessions). Sensitivity analyses will be carried out using the intention-to-treat principle to check the robustness of the results. Missing data will be replaced using multiple account imputation. Despite the randomization, we will attempt to minimize potential confounding by adjusting for baseline values and other potential confounders. The association between changes in ovarian function with changes in the mechanisms involved (secondary objectives 4, 5, and 6) will be analysed using Pearson or Spearman correlations and/or regression analysis. The analyses will be conducted with Stata v.13.1 or superior (StataCorp LP, College Station, TX). Statistical significance will be set at *P* < .05.

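### The planned change-score correlations cannot attribute mechanism changes to exercise, because variation in surgical weight loss can produce them without any exercise effect

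*Protocol article*

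**What the plan says.** At the end of the Introduction, the protocol article sets out the mechanism objectives. One asks whether "changes in inflammatory parameters, insulin resistance or arterial stiffness, induced by exercise, are associated with changes in ovarian function". Another asks how far changes in weight, body composition or fitness, "induced by the training program, are associated with changes in ovarian function will also be investigated". The background just before the aims lists as an open question "whether changes in these parameters can mediate possible improvements in women's ovarian function remain to be investigated".

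Section 2.11 refers to these as secondary objectives 4, 5 and 6 and says that the association "will be analysed using Pearson or Spearman correlations and/or regression analysis". The preceding sentence gives a general commitment: "we will attempt to minimize potential confounding by adjusting for baseline values and other potential confounders". Neither arm nor weight loss is named as a term for objectives 4 to 6.

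On timing, baseline is taken "within ∼12 days before the surgery" (section 2.6.1), and women are randomised "at medical discharge following bariatric surgery" (section 2.4). Every change score in both arms therefore spans the operation.

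**The concern.** The objectives concern a particular part of each change, the part that the training caused. A correlation between two change scores takes in all of the variation between women, whatever its source.

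The article itself names a strong common source. The Introduction says of surgery that "it significantly reduces excess weight", and that it brings remission of metabolic disease and seems to improve ovarian function. Section 2.6.2.1 expects SHBG to rise with weight loss. Section 2.6.3.3 treats a loss below 20% at 12 months as suboptimal, so the losses are large. Women who lose more weight may show larger falls in insulin resistance or inflammation and larger rises in SHBG, whether or not they trained.

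At stake is what a significant result would mean. The Discussion allows that surgical weight loss could explain a null trial. In that same trial the mechanism analysis could still give small P values, and the wording of the objectives would present them as effects of exercise.

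**Working it through.** **1. The plan's own figure.** Section 2.3 gives a difference of 10 nmol/L, SD 10, power 85% and α 0.05 (taken as two-sided).
- n per arm = 2 × (1.960 + 1.036)² × (10/10)² = 17.96, so 18 per arm and 36 in all.
- Allowing 10% loss: 36 / 0.90 = 40.
- Power at 18 per arm: Φ(√(18/2) − 1.960) = Φ(1.040) = 85.1%.
- Power at 20 per arm: Φ(√(20/2) − 1.960) = Φ(1.202) = 88.5%.

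All match the article. They concern the randomised comparison; the article gives no figure for the change-on-change analysis.

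**2. Model for the check.** Let W be standardised weight loss, M the mechanism change and Y the SHBG change. Exercise affects nothing, and M has no direct link to Y:
- M = a·W + √(1 − a²)·e₁
- Y = a·W + √(1 − a²)·e₂

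Then corr(M, Y) = a². The values of a are assumptions, because the article reports no such correlations. A mean shift common to all women adds a constant to M and Y and leaves the correlation unchanged. Only variation between women in W creates it.

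**3. Share of trials with P < .05 for the plain correlation, n = 36.** By Fisher's z: atanh(a²) × √33, compared with ±1.96.
- a = 0.3: r = 0.09; 0.0902 × 5.745 = 0.518; about 8%.
- a = 0.5: r = 0.25; 0.2554 × 5.745 = 1.467; about 31%.
- a = 0.6: r = 0.36; 0.3769 × 5.745 = 2.165; about 58%.
- a = 0.7: r = 0.49; 0.5361 × 5.745 = 3.080; about 87%.

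Simulation agrees. With 8,000 runs per setting the rates are 4.9% (a = 0), 8.3% (0.3), 32.6% (0.5) and 87.6% (0.7). A separate set of 5,000 runs gave 31.7% (0.5), 59.2% (0.6) and 87.3% (0.7). With unequal loadings of 0.3 and 0.5, the expected r is 0.15 and Fisher's z gives about 14%.

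**4. What adding terms does (8,000 runs, n = 36).**

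| a | Plain correlation | Regression + arm | Regression + weight loss | Regression + arm + weight loss | Between-arm test of Y |
|---|---|---|---|---|---|
| 0.3 | 8.3% | 8.2% | 5.4% | 5.3% | 5.1% |
| 0.5 | 32.6% | 31.8% | 5.0% | 5.0% | 5.0% |
| 0.7 | 87.6% | 86.5% | 5.2% | 5.2% | 4.9% |

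An arm term alone leaves the shared correlation in place. A weight-loss term removes it in this model, where weight loss is the only common cause and is measured without error. The randomised comparison stays at about its nominal level throughout.

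**5. What the model does not cover.** When weight or body composition is the candidate, W is the exposure or close to it, so its correlation with SHBG change is not spurious in this sense. The difficulty there is that surgical and exercise-induced loss are mixed in one change score.

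**The case against.** The article condenses a fuller plan, and covariates for secondary mechanism analyses are commonly left to that plan. Regression is offered as an option, and the adjustment sentence is broad enough to admit arm and weight loss. The objectives ask about association, and correlation is an ordinary way to study association. The high error rates depend on strong assumed loadings.

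Much of this stands, and it rules out several stronger readings that a reader might infer:
- That the plan pools the arms and ignores randomisation throughout. Section 2.11 does not say so. The absence of an arm term is certain only for the Pearson and Spearman options; for regression, no term is named either way.
- That the trial sets out to prove that mechanism changes drive ovarian function. The aims speak of association, and the mention of mediation sits in the background text.
- That surgery in every woman creates the correlation by itself. A shared shift does not; variation in weight loss can, and its strength is not given.
- That an arm term would be the whole cure. The table shows otherwise.
- That adjusting for weight loss is simply right. It is measured after randomisation, and section 2.7.1 cites evidence that concurrent training increases weight loss, so adjustment removes any exercise effect that acts through weight.

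What the objection does not remove is a mismatch within the stated text. The objectives attribute the changes to exercise, and a plain correlation, which fully meets the stated method, cannot support that attribution.

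**Conclusion.** The point holds in limited form. The analysis stated for objectives 4 to 6 can describe how changes move together after surgery, but it cannot show that the mechanism changes came from exercise. With no exercise effect and 36 women, a significant correlation would appear in about 8% to 87% of trials as the assumed correlation of both changes with weight loss goes from 0.3 to 0.7. At the low end this is close to the nominal 5%. The range rests on equal loadings, a single common cause and no direct link between mechanism and SHBG. The conclusion about attribution needs none of these values; it follows from the pre-surgery baseline and from the lack of an arm term in a plain correlation.

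The plan should be changed, but the reach is confined to these secondary objectives. The randomised comparison of SHBG is not touched by this point.

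**What to change.** - **Plain correlations:** report them only as descriptions of the post-surgical cohort, and drop the attribution to exercise from the objectives they serve.
- **Any exercise-mechanism statement:** fit two models. (i) Mechanism change on arm and baseline mechanism value. (ii) SHBG change on mechanism change, arm and baseline values. Report the indirect effect (arm coefficient in (i) × mechanism coefficient in (ii)) with a bootstrap interval, labelled exploratory.
- **Inflammation, insulin resistance, stiffness and fitness:** show the analysis with and without total weight loss. State that weight loss is post-randomisation and that adjusting for it removes any exercise effect acting through weight.
- **Weight or body composition as candidate:** state that the change-score association cannot separate surgical from exercise-induced loss.

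The cost is analysis wording; sections 2.6.3.1 to 2.6.3.4 already provide for the measurements. Intervals will be wide with about 36 women. The mediation estimate also relies on there being no unmeasured common cause of mechanism and SHBG change, which the trial cannot test and the report should state.

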### Registration and adherence to the SPIRIT standards

2.12

The study has been prospectively registered at the ISRCTN registry (ISRCTN27697878) on October 4, 2019, before the enrolment of participants begun (i.e., on October 15, 2019). This study adheres to the SPIRIT guidelines for randomized trials protocols^[93]^ and the results will be reported following the CONSORT standards (http://www.consort-statement.org/).

## Discussion

3

To the best of our knowledge, the EMOVAR study will assess, for the first time, the effects of a fully supervised concurrent exercise program initiated immediately after bariatric surgery, on ovarian function in severe/morbid obese women undergoing bariatric surgery. Previous studies demonstrate a U-shaped association of exercise with ovulation, with sedentary and over-trained women presenting higher incidences of anovulation.^[52]^ This relationship seems to be accentuated as BMI increases,^[52]^ underlining the importance of addressing the optimal dose of exercise. However, exercise prescription in morbid obese individuals is far from being well understood and little is known about the optimal dose of exercise in the morbid obese following bariatric surgery. We propose an evidence-based exercise intervention^[84]^ and describe it so that any agent involved in the management of morbid obese or bariatric patients can implement it in clinical practice, provided appropriate equipment and exercise professionals are available. This has been traditionally lacking in exercise-based clinical trials^[94]^ and opens a window of opportunity to translate exercise-based research into clinical practice. It is of course apparent that previous exercise-based literature in bariatric surgery individuals is clearly insufficient, and we recognize that some criteria are derived from studies carried out in non-morbid obese (nor bariatric surgery) individuals. For instance, the order of factors in the concurrent training (i.e., strength before aerobic training) was determined according to studies in obese (but not bariatric surgery) population, in which this order was the most beneficial for improving body composition, physical fitness and other health biomarkers.^[41]^ We also carried out a 2-week pilot exercise program to test the feasibility of some exercises in people with different characteristics who had undergone bariatric surgery in the prior weeks, which allowed our team adapting the initially prescribed program to the current structure.^[84]^ Therefore, the results of the EMOVAR clinical trial will have important clinical implications, not only for understanding the potential effects of exercise on ovarian function following bariatric surgery, but also for setting the bases of exercise prescription in this population.

Should the prescribed exercise program initiated immediately after bariatric surgery not have the expected beneficial effect on ovarian function, inflammation and arterial stiffness compared to usual care, the results of this clinical trial would still be of wide interest for the scientific community. These results could be explained by the great potential of bariatric surgery for improving weight loss during the first year following surgery. Should such unexpected results occur, this study would still contribute to the generation of new research ideas and hypotheses, such as modifying exercise program characteristics or combine it with other interventions such as nutritional or psychological treatments (or both), or extending the follow-up.

The trial results will be disseminated through international journals and other sources, without restrictions. Participants will receive personal information of their own results as well as a summary of the overall trial results.

### Study limitations/risks and contingency plan

3.1

Potential risk 1: EG patients do not attend the intervention.

Contingency plan: Different strategies will be implemented to maximize adherence to the exercise program. We will have a Contracted Personal Trainer with a Bachelor's or graduate degree in Physical Activity and Sports Sciences and a Master's in Personal Training, who has experience in training people with obesity. Each week, the EG participants will receive motivational messages via WhatsApp. In addition, at the start of each month, patients will receive a motivational video from the coaches and medical team through the same channels. The emotional state (The Feeling Scale) will be monitored and any adverse events that occur will be recorded during training. This will allow us to understand how they feel and offer alternatives.

Potential risk 2: Recruitment and/or retention rate are lower than planned.

Contingency plan: With the medical team involved, a large proportion of childbearing age women undergoing bariatric surgery in the province of Almería will be invited to participate in the study. If the rate of recruitment is not as expected, we would try to arrange new exercise training facilities (other than the University of Almería) in areas of the province where a greater number of participants could be included.
